### Stratification and randomization

Before randomization, YBCS (with and without high-risk relatives) will be stratified by self-reported race (black vs. other) to ensure equal distribution of ethnic minority participants across study arms. YBCS (n = 960 with high-risk relatives and n = 240 without high-risk relatives) will be randomly allocated to receive either the Targeted or the Enhanced Tailored version of the intervention via a computerized program generated by the study statistician. YBCS and high-risk relatives will be randomly assigned as a family unit.

### Targeted vs. enhanced tailored intervention

An expansion of the Theory of Planned Behavior (TPB) [14] was used as the framework to guide the development of the two versions of the intervention. The expanded TPB includes two additional components that are specific to the needs of YBCS and their high-risk relatives. The first component is knowledge about breast cancer risk factors and cancer genetics. The second component is perceived family support regarding breast cancer screening behaviors. Figure 3 shows the modified version of the TPB and the constructs hypothesized to be affected by the two versions of the intervention.

**Figure 3 F3:**
[figure not shown]
**Expanded theory of planned behavior.** CBE = Clinical Breast Exam.

Development of the Targeted version is based on a mailed intervention recommended by the Guide to Community Preventive Services as efficacious in increasing breast cancer screening among older, non-adherent women [15]. Participants randomized to the Targeted version will receive a personalized letter and a booklet that addresses breast cancer screening and genetic counseling in YBCS and high-risk relatives. The Enhanced Tailored version of the intervention will provide tailored information about 1) breast cancer risk; 2) adherence to screening and perceived barriers; and 3) ways to enhance family support related to breast cancer screening. Based on participants’ responses to the baseline survey, the study team will add evidence-based components to address the specific needs of YBCS and their high-risk female relatives that will be randomized to receive the Enhanced Tailored version. All the components that comprise the two versions of the mailed intervention are shown in Figure 4. All intervention materials are developed at the 9^th^ grade reading level or less.

**Figure 4 F4:**
[figure not shown]
**Components of the targeted and the enhanced tailored version of the intervention.** CA = Cancer.

Tailored health messages have the greatest advantage over targeted messages when there is significant variability within the targeted audience on key determinants of the intended outcome, e.g., knowledge and attitudes [16]. When there is little variability on the key determinants of the intended outcome, targeting could be as effective as tailoring and more cost-effective. In the case of screening mammography, two meta-analyses reported that although tailored interventions are more efficacious compared to non-tailored ones in increasing mammography screening [17,18], reminder-type, targeted interventions could also be efficacious in promoting repeated use of mammography [19]. Given that tailored interventions require a pre-existing mechanism for gathering data from the target population [16] they demand more resources making their routine implementation less likely. The present study will provide information on the level of variability among hypothesized key determinants of breast cancer screening, namely, access barriers and lack of social/family support among YBCS and their high-risk relatives, and it will allow the comparison of the efficacy of each intervention version.

### Outcomes

A follow-up survey will be mailed to YBCS and their high-risk relatives nine months after the baseline survey to determine the effect of each intervention version on: a) utilization of breast cancer screening and genetic counseling; b) perceived barriers and facilitators to screening; c) self-efficacy in utilizing screening services; d) family support related to screening; e) knowledge of the genetics of breast cancer; and f) satisfaction with the intervention. Table 2 describes the concepts and variables of the study (left column), the instruments that will be used to measure these variables (middle column), and the assessment times (right column). Instruments have been previously validated with various populations (see references in Table 2). Completion of the baseline and the follow-up questionnaires takes approximately 45 min.

**Table 2 T2:** Variables, instruments and assessment times

**Concepts/variables**	**Instruments**	**Survivor**		**High-risk relative**	
		**Baseline**	**Follow up**	**Baseline**	**Follow up**
**Knowledge/Attitude**					
Perceived breast cancer risk	Perceived breast cancer risk [11,20]			√	√
Knowledge of breast cancer risk factors	Breast cancer risk factor knowledge index [11,21]	√	√	√	√
Knowledge of breast cancer genetics	Knowledge of breast cancer gene inheritance [22]	√	√	√	√
Perceived facilitators vs. barriers of mammography screening	Decisional balance scale for mammography [23,24]	√	√	√	√
**Subjective norms**					
Perceived family expectations about breast cancer screening	Adapted from Ajzen et al. [14]	√	√	√	√
Motivation to comply with family members’ expectations	Adapted from Ajzen et al. [14]	√	√	√	√
**Family support**					
Perceived family support for breast cancer screening	Social support for breast cancer screening [25]	√	√	√	√
**PERCEIVED CONTROL**					
Self-efficacy in utilizing breast cancer screening services	Self-efficacy for mammography, CBE, cancer genetic services [14]	√	√	√	√
**Intention**					
Intention to pursue mammogram, CBE, genetic counseling (when applicable)	Intention to pursue mammography, CBE, and cancer genetic services (when applicable) [14]	√	√	√	√
**Behavior**					
Current screening practices	Behavioral risk factors surveillance system [24]	√	√	√	√
**Other**					
Demographics/personal and family history	Behavioral risk factors surveillance system [26]	√		√	
Breast cancer risk (Gail model)	Breast cancer risk assessment tool [27]			√	√
Breast cancer risk (Claus model)	Claus breast cancer risk tables [13]				
Evaluation of the Acceptability of the Intervention	TBD by researchers		√		√

### Sample size (power analysis)

Data analyses to meet Aim 3 will require comparison of randomly assigned subsamples of the entire sample and make the most demand on the sample size. PASS software [28] was used to determine the number of participants needed to provide 80% power to detect a medium-small difference (d = 0.3) between means or between percentages (h = 0.3) using a two-tailed test with alpha of 0.05. A medium-small effect size (d = 0.3 or h = 0.3) is a typical effect size found in interventions aiming to increase screening mammography [17,18]. The result of power analysis was 176 participants per group or 352 in total. Assuming 35% attrition between baseline and follow up, 542 participants must be given the intervention to maintain this level of power. Given the initial target number for recruitment and the expected response and attrition rates, the study will recruit and maintain a large enough sample size to perform data analyses for Aim 3 (see Figure 3).

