### Statistical analyses

Analyses will be conducted separately for YBCS and high-risk relatives. A descriptive analysis of baseline data will provide screening utilization practices, perceived barriers and facilitators to screening, and other outcomes for YBCS and high-risk relatives. This will include tabulating counts and frequencies of variables including demographics, cancer history, screening history and perceived breast cancer risk. Bivariate analyses (using the Chi-square test for differences in proportions and *T*-test for differences in means) to assess the associations between demographic factors, clinical indications and screening practices will follow. We will stratify by using the Cochran-Mantel-Haenszel test to assess the association between family history, screening practices, genetic counseling/testing, and perceived facilitators/barriers while controlling separately for race/ethnicity, age-group, and time since diagnosis. Outcomes include both continuous and dichotomous measures. Means and standard deviations will be used to describe the results. Continuous measures taken only at post-test will be compared between the two intervention groups by simple t-tests. After assuming an autocorrelation of data r = .30, changes over time in continuous measures will be tested by paired t-tests. For dichotomous measures taken only at post-test, the rates in the two groups will be compared by logistic regression. The proportions in each group will be reported to describe the results. If a baseline version of the measure is available, logistic regression will be conducted on the post-tests with the pre-tests included as covariates. Chi-square tests will be conducted to test the changes over time. The above analyses will establish whether the groups are equivalent, determine whether post-tests differ between the two groups, and assess the significance of changes over time. To further meet Aim 3, regression analyses (linear or logistic) will be used to test which factors (beyond the intervention) predict obtaining breast cancer screening.

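### The sample size is tied to no named outcome or population, so the stated 5% error rate and 80% power attach to one unspecified comparison among many in Aim 3

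*Protocol article*

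**What the plan says.** Aim 3 (Background) sets out to compare the two versions on screening utilization and on further outcomes, in survivors and in their high-risk relatives. The Outcomes section says that the follow-up survey is "to determine the effect of each intervention version on: a) utilization of breast cancer screening and genetic counseling", and then lists five more groups without ranking them: barriers and facilitators, self-efficacy, family support, genetics knowledge and satisfaction. Table 2 divides these into further scales and, under intention, separates mammogram, clinical breast exam (CBE) and genetic counselling.

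Statistical analyses states: "Analyses will be conducted separately for YBCS and high-risk relatives". Continuous post-test measures are compared between arms by t-test and dichotomous ones by logistic regression. The section gives no order of testing and no significance level.

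Sample size (power analysis) gives 80% power for a "difference (d = 0.3) between means or between percentages (h = 0.3) using a two-tailed test with alpha of 0.05". It justifies 0.3 on the ground that this "is a typical effect size found in interventions aiming to increase screening mammography". The result is "176 participants per group or 352 in total", and then: "Assuming 35% attrition between baseline and follow up, 542 participants must be given the intervention".

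Two further statements decide who is in the Aim 3 comparison. Recruitment expects 240 YBCS without eligible relatives and analyses them as a separate group. Recruitment step 5 removes an estimated 100 YBCS with a known hereditary syndrome from Aim 3.

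**The concern.** A sample size is a statement about one comparison: one outcome, one population, one alpha. Here the wording lets the comparison be any scale mean or any behaviour rate, in either population. Two things follow.

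First, the 80% power cannot be checked against the result that will be presented as the finding of Aim 3, because the plan does not say which result that is. Screening alone could mean mammography, CBE or genetic counselling.

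Second, the 5% error rate used to size the trial does not carry over to an efficacy conclusion that may be drawn from several comparisons. The result to emphasise could be chosen after the data are seen.

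**Working it through.** **Inputs.** From Sample size (power analysis): two-sided alpha 0.05, power 80%, d or h = 0.3, attrition 35%. From Outcomes: 6 outcome groups, or 5 without satisfaction, which is an acceptability measure. From Statistical analyses: 2 populations. From Recruitment: 604 relatives, 960 YBCS with relatives, about 100 YBCS excluded. Assumed here: the correlations between outcomes, and independence of the two populations.

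**Step 1. The plan's own figure.** n per group = 2(1.96 + 0.8416)² / 0.3² = 174.4, so 175 by the normal approximation. The noncentral-t calculation gives 175.4, so 176. Two groups make 352, and 352 / 0.65 = 541.5, so 542. The stated figures reproduce for a single comparison at 0.05.

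**Step 2. What h = 0.3 means for different outcomes.** Take the Michigan survey rates in Background (high-risk women over 40) as illustrative base rates, with p₂ = sin²(arcsin√p₁ + 0.15):
- mammogram: 48% to about 63%
- CBE: 56% to about 70%
- genetic counselling: 12% to about 23%

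One power statement thus covers quite different claims.

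**Step 3. Error rate if each comparison is made at 0.05.** With k independent tests the chance of at least one false positive is 1 − 0.95^k:
- k = 6 (one population): 26%
- k = 10 (satisfaction excluded, two populations): 40%
- k = 12 (all six groups, two populations): 46%

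Outcomes within a person are correlated, so these are upper figures for their counts. The table simulates equicorrelated normal test statistics (400,000 draws), with the two populations independent:

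| Within-population correlation (assumed) | 12 tests | 10 tests |
|---|---|---|
| 0.3 | 42% | 37% |
| 0.5 | 37% | 33% |
| 0.7 | 30% | 27% |
| 0.9 | 21% | 19% |

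**Step 4. Ways to repair it.** Powers are at d = 0.3 by noncentral t, with individuals treated as independent.
- One primary outcome in one population: 176 per group, unchanged.
- One primary outcome in each population, Bonferroni at 0.025: 213 per group, 426 completers and 656 recruited per population. Only 604 relatives are expected, and 604 × 0.65 ≈ 392 would complete, for 76% power.
- Bonferroni over 12 tests: 308 per group, 616 completers. Power at 176 per group falls to 47%.
- Fixed sequence, each step at 0.05: with 960 − 100 = 860 YBCS (taking all exclusions from those with relatives), 860 × 0.65 = 559 complete and power is 94%. With 392 relatives it is 84%. Power for both claims is about 0.943 × 0.842 = 0.79 if the two results are independent.

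**The case against.** The strongest reply is that screening is plainly the main interest, and much of this stands. Aim 3 names it first, the effect size comes from mammography interventions, and the closing Aim 3 regressions predict obtaining screening. In the expanded Theory of Planned Behavior, knowledge, norms, support and perceived control are determinants of behaviour. A reader might infer that the plan holds six outcomes of equal rank; it does not. What the text still lacks is one behaviour, in one population, called primary and linked to the calculation.

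A reader might also infer that the plan prescribes 0.05 for every test and would call a version superior on any one significant result. Neither is stated. Alpha appears once, as an input to the power calculation; applying it to each test is an inference, and no decision rule for superiority is given.

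Nor does the absence of a multiplicity procedure count by itself. This is a condensed article, and such a procedure may sit in an analysis plan that is not shown. The point rests on the sample-size section, which is shown and leaves its comparison open.

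Finally, it is tempting to quote 46%, or more with screening split into its components. Such figures assume independent tests and count satisfaction as an efficacy outcome, so they are ceilings for their counts rather than estimates.

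**Conclusion.** The point holds. The arithmetic of 176, 352 and 542 is right, but it applies to one comparison that the protocol does not identify. If the Aim 3 comparisons are each made at 0.05, the chance of at least one false-positive difference is about 33% for 10 tests at a correlation of 0.5. For 12 tests it is 21% to 42% over correlations of 0.9 to 0.3, with 46% as the limit under independence. These figures depend on three assumptions: 0.05 per test, the chosen correlations, and independence between survivors and relatives. Over the whole range examined, the rate is at least about four times the nominal 5%. The matter should be corrected, and wording is enough to do it.

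**What to change.** 1. Name one primary screening outcome at follow-up and tie the h = 0.3 calculation to it, with the assumed base rate. Mammography use is the natural candidate because the effect size comes from mammography interventions; another single screening outcome would serve if the sponsor prefers it.
2. Name the primary population among the YBCS eligible for Aim 3. Exclude those with known hereditary syndromes, as Recruitment step 5 requires, and say how the separately analysed YBCS without relatives are handled.
3. Test that population at two-sided 0.05. Test the relatives at 0.05 only if the first test is significant, with the order stated in advance.
4. Label all other outcomes secondary, reported with confidence intervals and with no efficacy claim of their own.

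The cost is protocol wording; the sample size stays as it is. The price is that a formal claim in relatives depends on the survivors' result, which takes its power from about 84% to about 79% under the assumptions above.

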### Statistical analyses

Analyses will be conducted separately for YBCS and high-risk relatives. A descriptive analysis of baseline data will provide screening utilization practices, perceived barriers and facilitators to screening, and other outcomes for YBCS and high-risk relatives. This will include tabulating counts and frequencies of variables including demographics, cancer history, screening history and perceived breast cancer risk. Bivariate analyses (using the Chi-square test for differences in proportions and *T*-test for differences in means) to assess the associations between demographic factors, clinical indications and screening practices will follow. We will stratify by using the Cochran-Mantel-Haenszel test to assess the association between family history, screening practices, genetic counseling/testing, and perceived facilitators/barriers while controlling separately for race/ethnicity, age-group, and time since diagnosis. Outcomes include both continuous and dichotomous measures. Means and standard deviations will be used to describe the results. Continuous measures taken only at post-test will be compared between the two intervention groups by simple t-tests. After assuming an autocorrelation of data r = .30, changes over time in continuous measures will be tested by paired t-tests. For dichotomous measures taken only at post-test, the rates in the two groups will be compared by logistic regression. The proportions in each group will be reported to describe the results. If a baseline version of the measure is available, logistic regression will be conducted on the post-tests with the pre-tests included as covariates. Chi-square tests will be conducted to test the changes over time. The above analyses will establish whether the groups are equivalent, determine whether post-tests differ between the two groups, and assess the significance of changes over time. To further meet Aim 3, regression analyses (linear or logistic) will be used to test which factors (beyond the intervention) predict obtaining breast cancer screening.

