### Recruitment of YBCS and high-risk relatives

Between 1994 and 2008 there were 9,000 cases of young women with breast cancer were reported to the Michigan Cancer Registry. For the study, 3,000 women diagnosed with invasive or in –situ-breast cancer between 20 to 45 years old from 1994 to 2008 will be randomly selected from the cancer registry database. The Michigan Cancer Surveillance Program will cross-reference mortality data to exclude deceased YBCS. To increase inclusion of minority and underserved women, the sample will be stratified by race. The study will oversample YBCS who are black and living in counties with the highest mortality rates for young women with breast cancer (See Figure 1).

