**Figure 2 F2:**
[figure not shown]
**CONSORT diagram-flow of study participants.** Est. = Estimated.

**Table 1 T1:** Eligibility criteria

**Eligibility criteria for young breast cancer survivors**	**Eligibility criteria for high-risk female relatives**
• Female	• Female
• 25–64 years of age	• 25–64 years of age
• Being diagnosed with unilateral or bilateral invasive breast cancer between 20 and 45 years old	• Unaffected with any type of cancer
• Being diagnosed with unilateral or bilateral DCIS^ж^ between 20 and 45 years old	• First- or second-degree relatives of the YBCS
• Michigan resident at time of diagnosis	• US resident
• Able to read and understand English	• Able to read and understand English
• Not currently pregnant, incarcerated, or institutionalized*	• Not currently pregnant, incarcerated, or institutionalized*
	• YBCS is willing to contact

^ж^ Ductal Carcinoma In Situ.

* Women who are pregnant, incarcerated, or institutionalized at the time of the study are excluded because they may not be able to follow recommendations for breast cancer screening and genetic counseling.

Recruitment procedures will involve the following steps:

1) Obtain approval to conduct research with human subjects from the Institutional Review Boards at the University of Michigan and at the Michigan Department of Community Health, and the Scientific Advisory Board of the Michigan Cancer Registry.

2) The cancer registry will send a letter to the reporting facility and the physician of record asking if they are aware of any reason that the YBCS should not be contacted to participate in the study. The YBCS will be excluded from the study if the reporting facility or physician of record responds to this letter requesting that the YBCS not be contacted.

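### Baseline associations are adjusted for race, age group and time since diagnosis one at a time; if more than one of these confounds, each result keeps confounding that a joint model would largely remove

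*Protocol article*

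**What the plan says.** In the protocol article, Statistical analyses, the baseline data are first described, then examined by bivariate tests, and then by a stratified test. The Cochran-Mantel-Haenszel test is to "assess the association between family history, screening practices, genetic counseling/testing, and perceived facilitators/barriers", and this is done "while controlling separately for race/ethnicity, age-group, and time since diagnosis". The section also states: "Analyses will be conducted separately for YBCS and high-risk relatives".

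The section closes with a model under Aim 3: "regression analyses (linear or logistic) will be used to test which factors (beyond the intervention) predict obtaining breast cancer screening". No covariates are listed for it.

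Three features of the sampling bear on the point:
- Survivors are women diagnosed "between 20 to 45 years old from 1994 to 2008 will be randomly selected from the cancer registry database" (Recruitment of YBCS and high-risk relatives).
- Table 1 in the same section limits entry to "25–64 years of age".
- To increase inclusion of minority women, "the sample will be stratified by race", with oversampling of black survivors living in high-mortality counties.

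The article does not say whether age group in the stratified tests is current age or age at diagnosis.

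**The concern.** By naming three factors to control, the plan treats all three as possible confounders. A test stratified on one of them does nothing about the other two, except where they are correlated with the one controlled. Each question then gets up to three partly adjusted answers, which may disagree, and the article gives no rule for choosing among them.

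At stake is how the baseline findings are read, for example whether women with a stronger family history use counselling more, or whether perceived barriers go with lower screening. The Discussion expects the findings to apply to survivors and relatives across Michigan, so a reader may take an adjusted association at face value when it is only partly adjusted.

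**Working it through.** **Plan's own figures.** The article states no figure for these baseline tests. Its only calculated figure is the Aim 3 sample size. That reproduces: a two-sample t-test with d = 0.3, 80% power and two-sided alpha 0.05 needs 175.4, so 176 per group and 352 in total; 352 / (1 − 0.35) = 541.5, so 542. The present point does not affect it.

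**Step 1: are age and time since diagnosis related?** For a survivor, current age = age at diagnosis + time since diagnosis. With diagnosis no later than age 45, a woman aged 55 is at least 55 − 45 = 10 years past diagnosis.

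From the documents: age at diagnosis 20–45, diagnosis 1994–2008, current age 25–64. Assumed: diagnosis dates uniform over the window; survey in 2011, 2012 or 2013 (the article gives no year); age at diagnosis either uniform or weighted to older ages (20 + 26 × a Beta(4, 1.3) variable). Simulating 1,000,000 survivors gives:

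| Correlation with time since diagnosis | Uniform age at diagnosis | Older-weighted |
|---|---|---|
| Current age | 0.49 to 0.50 | about 0.70 |
| Age at diagnosis | −0.02 to 0.00 | about 0.00 |

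The relation exists only if age group means current age.

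**Step 2: what does single-factor control leave?** Assumed for illustration: survey in mid-2012; 30% black, independent of age and time; current age cut at 35, 45 and 55; time cut at 8 and 13 years. Two binary variables X and Y are generated independently given the three factors, so the true odds ratio is 1:

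logit P(X) = −0.3 + b·z(age) + b·z(time) + b·black

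logit P(Y) = −0.1 + b·z(age) + b·z(time) + b·black

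Here z() is the standardised value. The Mantel-Haenszel odds ratio is Σ(a·d/N) / Σ(b·c/N) over strata, where a, b, c, d are the four cells of each stratum's table. Joint control uses 2 × 4 × 3 = 24 strata. Each cell below gives uniform / older-weighted.

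| Assumed log-odds | Crude | Race only | Age only | Time only | Joint |
|---|---|---|---|---|---|
| 0 for all | 1.00 / 1.00 | 1.00 / 1.00 | 1.00 / 1.00 | 1.00 / 1.00 | 1.00 / 1.00 |
| 0.2 each | 1.13 / 1.14 | 1.12 / 1.14 | 1.05 / 1.05 | 1.05 / 1.04 | 1.01 / 1.01 |
| 0.3 each | 1.30 / 1.34 | 1.29 / 1.32 | 1.11 / 1.12 | 1.12 / 1.10 | 1.02 / 1.03 |
| 0.5 each | 1.87 / 1.97 | 1.82 / 1.92 | 1.33 / 1.32 | 1.32 / 1.26 | 1.06 / 1.07 |
| 0.5, time only | 1.26 / 1.26 | 1.26 / 1.26 | 1.20 / 1.15 | 1.03 / 1.03 | 1.03 / 1.03 |

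The small remainder under joint control reflects the width of the age and time groups.

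**Step 3: reading the table.** When several factors confound, every single-factor column stays above the joint column. When only time confounds, control for time alone does as well as joint control. In that last row, age-only control leaves 1.20 where the correlation of age and time is about 0.5, and 1.15 where it is about 0.7. A stronger tie means that control for one factor removes more of the bias from the other.

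**Step 4: price of joint adjustment.** With correlation r between two terms in a linear model, the variance of each is inflated by 1 / (1 − r²). For r = 0.5 this is 1 / 0.75 = 1.33 (standard error × 1.15); for r = 0.7 it is 1 / 0.51 = 1.96 (standard error × 1.40). This falls on the coefficients of age and time themselves, which are adjustment terms here.

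**The case against.** The strongest reply is that this is exploratory work. Aims 1 and 2 ask for screening status, barriers and facilitators, and willingness; neither names an adjusted association. One-at-a-time stratified tables are a common first step, and a condensed article may leave covariate lists to a fuller plan. That limits the importance of the point but does not answer it, because the article does not merely omit a joint model here: it specifies separate control. The closing regression does not clearly fill the gap either. It is placed under Aim 3 and models only obtaining screening, so associations with counselling or testing, or with barriers and facilitators, are not covered.

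A reader might also infer stronger criticisms that the documents do not support:

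- **That the sampling ties age to time since diagnosis and so leaves each result confounded.** The tie holds only for current age, and the article does not define age group. Nor is the tie the cause: an omitted confounder biases a result even when unrelated to the controlled one, and correlation lets control for one factor absorb part of the other's effect.
- **That no single-factor test removes confounding.** This is conditional. If only one factor confounds, controlling that factor suffices; if none does, there is nothing to remove.
- **That oversampling by race creates confounding.** It changes how many black survivors are sampled. It does not by itself link race to age, time since diagnosis or screening.
- **That the barrier and facilitator scales must be dichotomised.** The Cochran-Mantel-Haenszel family includes mean-score and correlation statistics that accept ordered scores, and the article does not say which form is meant.
- **That relatives are affected in the same way.** They are free of cancer and have no time since diagnosis of their own. For them the issue is race and age only.

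**Conclusion.** The point holds in a limited form. The article fixes one-at-a-time control for its baseline associations and states no joint adjustment for them. If at least two of the three named factors confound an association, each single-factor result keeps residual confounding. Under the assumed 0.3 log-odds per factor, the spurious odds ratio is about 1.1 (age or time controlled) to 1.3 (race controlled); over 0.2 to 0.5 it runs from 1.04 to 1.33 for age or time and from 1.12 to 1.92 for race, against 1.01 to 1.07 with joint control.

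These sizes rest wholly on assumed confounder effects and distributions, since the documents report none; they show what is possible, not what will be found. The consequence is confined to the interpretation of exploratory baseline associations. The comparison of the Targeted and Enhanced Tailored versions is untouched. This is a worthwhile improvement, not a threat to the trial.

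**What to change.** In Statistical analyses, make the adjusted analysis of each baseline association a single regression: logistic where the outcome is screening or counselling/testing, linear where it is a scale score. Enter race/ethnicity and age together, and add time since diagnosis in the survivor models only. State whether age group is current age or age at diagnosis. Keep the separate stratified tables as description.

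The cost is small. The article already plans to use these variables, so no data collection is added. Results become model estimates, which need a sentence more of explanation than a stratified test. If current age is used, the age and time terms will be less precisely estimated because they overlap.
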